### Safety assessments

The participants’ blood, urine, stool routine, liver and kidney function, electrocardiogram and chest X-ray will be monitored at baseline and weeks 24, 48 and 72 during the treatment period.

### Adverse event and oversight

Investigators will ask every subject at each visit whether they have experienced any adverse events (AEs) during the study period. If they have any AEs, the investigator will provide appropriate treatment to the subject immediately and record the AEs. In the case of serious adverse events (SAEs), the investigator will offer appropriate treatment to the subject immediately and report the event to the First Affiliated Hospital of Henan University of Chinese Medicine within 24 h from the time of recognition. If necessary, blinding will be broken by adequate procedure, and the documented procedure will be kept in the investigator’s study file. Any adverse events during the trial will be recorded in detail.

The oversight is in charge of Guangzhou Boji Contract Research Organization (CRO), through quarterly independently monitoring by clinical research associates (CRA) in terms of safety, quality and progress of the study.

### Sample size

A pilot experiment we performed showed that the incidence of endpoint events in the control group was 35%, and the incidence of endpoint events in the TCM group was 8%. Therefore, the required sample size is 33 cases in the control group and 66 cases in the treatment group. According to the preliminary project research and considering the typical 10% dropout rate of patients who participate in therapy, the final required sample size for the trial is 216 cases.

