## Methods/design

### Study design

This will be a multicentre, randomised, double-blind, simulated, parallel-controlled clinical trial. Participants will be recruited from six centres: Shanghai Public Health Clinical Centre; Beijing Ditan Hospital, Capital Medical University; Sichuan Academy of Chinese Medical Sciences; Ruikang Hospital Affiliated to Guangxi University of Chinese Medicine; Kunming Municipal Hospital of Traditional Chinese Medicine; and the First Affiliated Hospital of Henan University of Chinese Medicine. The study schema and estimated recruitment numbers are presented in Fig. 1. Eligible participants will be randomised to be assigned to the test group (TCM groups) or control groups (placebo) in a 1:1 ratio. Both groups will undergo a treatment period of 72 weeks and a follow-up period. Nineteen visits will be scheduled for each patient: baseline and each 4 weeks, 4, 8, 12, 16, 20, 24, 28, 32, 36, 40, 44, 48, 52, 56, 60, 64, 68 and 72.

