### Randomisation and blinding

Centralised randomisation was carried out by the Institute of Basic Research in Clinical Medicine, China Academy Of Chinese Medical Sciences, using the Clinical Research System (CRS), a remote electronic data capture. When an eligible participant is enrolled, the CRC has to register the detailed information of the participant on CRS. Then, after the confirmation of the investigator, the participant will be assigned to either the test or control groups in an allocation ratio of 1:1. The CRS will automatically generate the participant’s ID numbers and feedback to the investigator.

This trial is a double-blind trial in which the participants and investigators are blinded. The patients will receive a TCM drug or placebo.

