### Statistical analysis

All statistical analyses will be performed using SAS 9.0. All statistical tests will be two-sided, and *P* < 0.05 will be considered statistically significant. Baseline information, such as mean, standard deviation and minimum and maximum values, will be calculated to describe the quantitative indicators. Categorical indicators will be described by frequency. For the analysis of efficacy and safety indicators, Cox survival analysis will be used to compare the time to endpoint events between the two groups, and TCM symptoms will be analysed using the chi-square test or rank-sum test.

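### The stated requirement of 33 control and 66 treated patients contradicts the 1:1 randomisation, and the total of 216 cannot be derived from the stated inputs

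*Protocol article*

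**What the plan says.** All inputs are in the protocol article.

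- **Planning effect (Sample size).** From a pilot, "the incidence of endpoint events in the control group was 35" per cent and "the incidence of endpoint events in the TCM group was 8" per cent.
- **Intermediate result (Sample size).** "the required sample size is 33 cases in the control group and 66 cases in the treatment group".
- **Adjustment (Sample size).** The text refers to earlier research within the project, without giving a figure from it, and continues "considering the typical 10% dropout rate of patients who participate in therapy".
- **Final figure (Sample size).** "the final required sample size for the trial is 216 cases".
- **Allocation.** Study design has patients "assigned to the test group (TCM groups) or control groups (placebo) in a 1:1 ratio". Randomisation and blinding has them "assigned to either the test or control groups in an allocation ratio of 1:1".
- **Test level (Statistical analysis).** "All statistical tests will be two-sided", with significance at P < 0.05.

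The Sample size section gives neither the power nor the formula.

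**The concern.** Two printed statements conflict with the rest of the plan. First, the required numbers put twice as many patients on treatment as on control, but the trial allocates equally. Second, the only quantified adjustment between the intermediate result and the final figure is 10% dropout, and that cannot turn 99 into 216.

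The sample size is the stated reason for enrolling 216 people who are not on antiretroviral therapy for 72 weeks of TCM or placebo. If the printed assumptions are the real ones, about half that number would do. If 216 rests on something else, the article does not say what. Either way, a reader cannot check the figure.

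**Working it through.** **Inputs.** p₁ = 0.35 (control), p₂ = 0.08 (TCM), difference 0.27, dropout 10%, two-sided alpha 0.05. Power is not stated, so 80% to 90% is assumed.

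**Step 1: can 33/66 be reproduced?** With r treated patients per control, the pooled formula for the control arm is

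n = [1.960·√(p̄(1−p̄)(1+1/r)) + z_β·√(p₁(1−p₁) + p₂(1−p₂)/r)]² / (p₁−p₂)², where p̄ = (p₁ + r·p₂)/(1+r).

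At r = 2, p̄ = 0.17. At 90% power, n = (0.9017 + 0.6588)²/0.0729 = 33.4, so the treated arm is 66.8. This gives 33/66 only by rounding down; rounding the control arm up gives 34/68. Other routes also lead to 33:

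| Ratio | Formula | Power | n (control arm) | Reading of 33 and 66 |
|---|---|---|---|---|
| 1:2 | pooled | 90% | 33.4 | 33 control, 66 treated (rounded down) |
| 1:2 | arcsine | 90% | 32.9 | 33 control, 66 treated |
| 1:2 | unpooled | 85% | 32.6 | 33 control, 66 treated |
| 1:1 | unpooled | 80% | 32.4 | 33 per arm, 66 in total |
| 1:1 | arcsine | 80% | 32.7 | 33 per arm, 66 in total |

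So 33/66 may come from a 1:2 calculation, or from a 1:1 calculation whose total was labelled as the treatment group. The article does not settle which.

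**Step 2: from 99 to 216.**

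- 33 + 66 = 99; 99/0.9 = 110; 99 × 1.1 = 108.9, so 109.
- Reaching 216 from 99 by dropout alone would need 1 − 99/216 = 54%.
- Setting both arms to 66 gives 132, and 146 to 147 with 10% dropout.

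None of these gives 216.

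**Step 3: what the stated effect needs at 1:1.** Here p̄ = 0.215 (pooled formula).

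- 80% power: (1.1387 + 0.4618)²/0.0729 = 35.1, so 36 per arm, 72 in total; 72/0.9 = 80.
- 90% power: (1.1387 + 0.7032)²/0.0729 = 46.5, so 47 per arm, 94 in total; 94/0.9 = 104.4, so 105.

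Against these, 216 is 2.7 times (216/80) and 2.1 times (216/105) the requirement. Across the unpooled, arcsine, pooled and continuity-corrected formulas at 80% to 90% power, the 1:1 total before dropout runs from 66 to 108. Even the largest becomes only 108/0.9 = 120.

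**Step 4: what 216 delivers at 1:1.** 216/2 = 108 per arm, and 108 × 0.9 ≈ 97 after dropout.

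- 35% v 8%: z = (√97 × 0.27 − 1.1387)/0.5487 = 2.77, so power is 99.7%. With all 108 per arm it is 99.9%.
- With 97 per arm, power is about 90% for 35% v 15% and 80% for 35% v 17.4%. These two contrasts are solved backwards from 216 and do not appear in the article.

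**The case against.** The best defence is that dropout is not the only ground given for 216: the same sentence also invokes earlier project research. That is fair, and it is why the finding is that 216 cannot be derived from the stated inputs, rather than that it has no basis. But no number or multiplier is attached to that research, so the step remains untraceable.

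A related defence supplies the missing step. If 33 is per arm and 66 the two-arm total, 66 plus 10% is about 72, and three TCM syndromes give 3 × 72 = 216. The arithmetic works, but it is conjecture. The text assigns 66 to the treatment group and mentions no sizing by syndrome. The Interventions section also treats the TCM regimens as one overall intervention and has the syndrome type re-diagnosed before each cycle. If this was the intent, the paragraph is still misstated.

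That a journal article condenses its protocol does not help either. The inputs, intermediate result and final figure are all printed, and they conflict.

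Three stronger readings are tempting but not supported:

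- **That the trial is too small, or that a null result could not be interpreted.** The planning effect is stated, and 216 has over 99% power for it.
- **That sizing on incidence is wrong because a Cox model is planned.** Primary outcome measure names endpoint event incidence alongside time to endpoint events, so incidence is a named primary measure.
- **That a 1:2 calculation at 90% power is the proven source of the error.** Step 1 shows it is only one of several candidates.

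**Conclusion.** Wrong as written. The 33/66 requirement contradicts the 1:1 allocation stated in two other sections, and 10% dropout takes 99 to 109 or 110, not 216. Nothing elsewhere in the article reconciles these figures.

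Both contradictions hold whatever power or formula was used. The size of the excess depends on assumptions. With two-sided 5%, the pooled formula and 1:1, 216 is about twice the need at 90% power and 2.7 times at 80%. The error therefore does not weaken the trial's ability to detect 35% v 8%. It leaves the enrolled number without a justification that can be checked.

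**What to change.** Rewrite the Sample size paragraph in three parts.

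1. Replace the 33/66 statement with a 1:1 calculation that gives alpha, sidedness, power and formula. With the pooled formula this is 36 per arm (80% power) or 47 per arm (90% power) for 35% v 8%.
2. Show the actual step to 216, including any multiplier taken from the earlier project research. Only the sponsor can supply this.
3. State what 216 delivers at 1:1 after 10% dropout (97 per arm): over 99% power for 35% v 8%. For information, it also gives about 90% power for 35% v 15% and 80% for 35% v 17.4%. These last two must not be presented as the reason 216 was chosen.

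The cost is one paragraph of wording and a check of the sponsor's sample size records. Enrolment, allocation and conduct do not change.

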### Statistical analysis

All statistical analyses will be performed using SAS 9.0. All statistical tests will be two-sided, and *P* < 0.05 will be considered statistically significant. Baseline information, such as mean, standard deviation and minimum and maximum values, will be calculated to describe the quantitative indicators. Categorical indicators will be described by frequency. For the analysis of efficacy and safety indicators, Cox survival analysis will be used to compare the time to endpoint events between the two groups, and TCM symptoms will be analysed using the chi-square test or rank-sum test.

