#### Secondary outcomes

The secondary outcomes are as follows:Common symptom and TCM syndrome score: The effectiveness of TCM is evaluated using the common symptom sore method (Table 4) and the TCM syndrome sore method (Table 5). According to Guiding principles for clinical research of new drugs of TCM (Trial) (2002) [14], a reduction in TCM syndrome score by ≥ 30% indicates that the clinical symptoms improved or disappeared and the treatment is considered clinically effective. The TCM syndrome score is calculated as follows: [(scores before treatment − scores after treatment)÷scores before treatment] × 100%.Virological load: HIV virological load (VL) will be done at baseline and week 72 during the follow-up. According to and TCM diagnosis and treatment criteria for HIV/AIDS [15], ratings are effective, invalid and steady.Immunological indicators and inflammatory factors: CD4+ cell count, CD8+ cell count and CD4/CD4 will be done at baseline and weeks 12, 24, 48, 60 and 72 during the treatment period. According to and TCM diagnosis and treatment criteria for HIV/AIDS [15], ratings are effective, invalid and steady. Changes in inflammatory factors (IF) include interleukin(IL)-17, IL-4, tumour necrosis factor (TNF)-a, interferon-γ (INF-γ) and immunological indicator(II) including natural killer cell (NK), CD4+CD45RA+T lymphocytes, and CD4+CD45RO+T lymphocytes will be done at weeks 0 and 72 of the follow-up phase.Quality of life (QOL) and patient-reported outcomes (PRO): Assessment of the quality of life of PHIV by using the WHOQOL-HIV-brief [16]  and Patient Peport Outcomes Assessment Scale (PLWHA-PRO) [17]. They will be observed and recorded prior to treatment, at baseline and weeks 24, 48 and 72 of the follow-up phase.

**Table 4 Tab4:** Evaluation criteria of common symptoms

Symptoms	Score		
	Mild = 3	Moderate = 6	Severe = 9
Fever	T ≤ 38.0 °C	38.0 °C < T < 38.5 °C	T ≥ 38.5 °C
Cough	Intermittent cough during the day	Intermittent cough during the day and occasionally at night	Frequent cough day and night
Expectoration	Expectoration 10-50 ml or expectoration 5-25 ml at night and morning	Expectoration 50-100 ml or expectoration 5-25 ml at night and morning	Expectoration > 100 ml or expectoration 50-100 ml at night and morning
Weight loss	Weight loss ≤ 10%	10% < weight loss < 20%	Weight loss ≥ 20%
Cold	≤ 2 times/month or 1 time/2 weeks	3-4 times/month or 1 time/week	≥ 5 times/month or > 1 time/week

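### Cutting the TCM score, CD4 and viral load into response classes, with no baseline-adjusted analysis of the uncut values, would cost power on these secondary outcomes

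*Protocol article*

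**What the plan says.** In the protocol article, Secondary outcomes defines a fall of at least 30% in the TCM syndrome score, as a percentage of its pre-treatment value, as clinically effective. For viral load, and again for the CD4/CD8 measures, it says that "ratings are effective, invalid and steady", citing a TCM guideline for the criteria.

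Statistical analysis names two methods for efficacy:
- for the primary outcome, "Cox survival analysis will be used to compare the time to endpoint events between the two groups";
- for one secondary outcome, "TCM symptoms will be analysed using the chi-square test or rank-sum test".

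No test is given for CD4, CD8 or viral load. It is not stated whether the rank-sum test would use the numeric TCM score or a class made from it. No covariate is named for the Cox model, and none is ruled out.

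Table 3 schedules the TCM syndrome score at baseline and 18 later visits, CD4 at baseline and six later visits, and viral load at baseline and week 72.

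**The concern.** A class such as response or non-response treats a patient who just passes the cut and one who passes it by far as the same. That lowers power at a fixed sample size. Chi-square needs classes, so one of the two tests named for TCM symptoms necessarily works on cut data. Neither test takes the baseline value as a covariate, although a baseline correlated with the outcome would sharpen the comparison at no cost.

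The outcomes affected are secondary, but they carry the trial's evidence on symptoms, immune function and virology. A real effect of moderate size could be missed although the data to detect it had been collected.

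**Working it through.** **The plan's own figures.** The protocol states no power for any secondary outcome, so there is none to reproduce. The Sample size section works from pilot event rates of 35% and 8% and says that "the required sample size is 33 cases in the control group and 66 cases in the treatment group". The pooled two-proportion formula at 2:1, two-sided 5% and 90% power gives 34 and 68, so those counts are consistent with an unstated 90% power. The step from 33 + 66 = 99 to 216 does not follow (99 / 0.90 = 110). That is a separate matter; here 216 is taken as given.

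**Inputs from the protocol.** Total 216, allocation 1:1, 10% dropout: 108 × 0.90 = 97.2, so about 97 evaluable per arm. Two-sided α = 0.05.

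**Assumptions.** The protocol gives no SD, effect size or correlation for these outcomes, and the rating cut-offs lie in a cited source. I assume a normal outcome, an effect with 80% power on the uncut value, and a baseline correlation r of 0.3 to 0.7. The standardised effect is d = (1.96 + 0.84) × √(2/97) = 0.40.

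**Power formula.** If an analysis retains a fraction k of the information in the uncut value, power = Φ(2.80 × √k − 1.96).

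1. Two classes with a proportion p on one side: k = φ(z_p)² / [p(1 − p)].
   - p = 0.5: k = 0.637, power 61%
   - p = 0.3: k = 0.576, power 57%
   - p = 0.2: k = 0.49, power 50%
2. Three ordered classes: k = Σ (φ(lower cut) − φ(upper cut))² / class probability. Thirds give 0.793; a 25/50/25 split gives 0.808. Power is 70–71%. This assumes a test that uses the ordering; a general chi-square on three classes would do worse.
3. Rank-sum on the uncut score: k = 3/π = 0.955, power 78%.
4. ANCOVA on the uncut value: k = 1/(1 − r²).
   - r = 0.3: k = 1.10, power 84%
   - r = 0.5: k = 1.33, power 90%
   - r = 0.7: k = 1.96, power 97%

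**Sensitivity.** Steps 1 and 2 equate a cut follow-up value with a cut change when r = 0.5. If the class is cut from the change from baseline, k is divided by 2(1 − r):

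| r | Two classes (even split) | Three classes (thirds) | ANCOVA |
|---|---|---|---|
| 0.3 | 47% | 56% | 84% |
| 0.5 | 61% | 70% | 90% |
| 0.7 | 82% | 90% | 97% |

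The gap narrows as r rises but keeps its direction.

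**Cox model.** The pilot rates imply a hazard ratio of ln(0.92)/ln(0.65) = 0.19 and 97 × (0.35 + 0.08) ≈ 42 events. Simulation (97 per arm, 35% control incidence, one standard-normal covariate, 1,500 runs per setting) gave:
- at hazard ratio 0.19: 99.2–99.9% unadjusted, 99.7–100% adjusted;
- at an assumed hazard ratio of 0.5, with a log hazard ratio per covariate SD of 0.3, 0.5, 0.8 or 1.0: 68, 66, 59 or 54% unadjusted, 69–70% adjusted. The gain is about 1 to 16 points.

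**The case against.** **The document is a condensed article.** Test specifications for CD4 and viral load, and covariate lists, are commonly left to a full protocol or SAP. This stands: their absence is not a defect. The point rests only on what is printed, namely the 30% cut, the three ratings, and chi-square or rank-sum for TCM symptoms. The loss on CD4 and viral load is therefore conditional on the ratings being the analysed variables.

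**A reader might infer that CD4 and viral load are tested by chi-square or rank-sum.** The text does not say so; those tests are given to TCM symptoms only. Nor does every efficacy outcome lose power. No cut is set for the common symptom total, quality of life or patient-reported outcomes, and cytokines and cell subsets are described as changes.

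**Rank-sum is defensible.** The scores are sums of items scored 0, 3, 6 or 9 in patients described as asymptomatic, so skew and floor effects are plausible. This stands. On the uncut score rank-sum loses only about 5% of the information; the damage comes from the cut and the unused baseline. The ANCOVA figures assume normality and may be optimistic for such scores.

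**A reader might infer that the Cox model is unadjusted and the primary analysis underpowered or biased.** The text is silent on covariates, and power at the pilot effect already exceeds 99%. An unadjusted hazard ratio nearer to 1 reflects non-collapsibility: it is a valid marginal effect with a valid test. Entry CD4 is limited to 250–500/μL, which may also reduce its prognostic value.

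**Conclusion.** The concern holds for the TCM syndrome score as far as the 30% responder is what is tested, and for CD4 and viral load if the ratings are what is analysed. Under the stated assumptions a two-class cut keeps 49–64% of the information and three ordered classes about 80%, while baseline adjustment of the uncut value adds to it. The direction is secure; the exact percentages rest on an assumed effect of 0.40 SD, assumed correlations and assumed cut positions.

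This is a matter of efficiency on secondary outcomes, not an error or contradiction in the plan. It does not show a weakness in the primary Cox comparison at the effect the trial was planned on.

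**What to change.** - **Main analysis of the TCM syndrome score, CD4 and log10 viral load:** a baseline-adjusted analysis of the uncut value. Use ANCOVA at week 72 or, for CD4 and the TCM score, a repeated-measures model with baseline as covariate and the contrast at week 72. Specify a rank-based ANCOVA if the scores are skewed or at the floor.
- **Supportive:** keep the 30% response and the effective/steady/invalid ratings, so the guideline convention is still reported.
- **CD4 visits:** before a repeated-measures model is fixed, reconcile Table 3, which includes week 36, with Secondary outcomes, which omits it.
- **Cox model, optional:** prespecify baseline CD4 and log10 viral load as covariates. About 42 events at the pilot rates argue for no more than these two. Do not stratify by the six centres: 42/6 is about seven events per centre, and nothing in the document calls for it.

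The cost is wording, a little more programming and a model assumption for the scores. No new data or visits are needed. The choice should be fixed before unblinding.

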## Discussion

Patients with AIDS remain a major public health problem. TCM as a system of medicine has been a form of health care in China for several thousand years. Many studies show that TCM can reduce anti-retroviral side effects, increase patients’ immunity, improve QOL and clinical symptoms and prolong patients’ life and is an effective and safe TCM in treating HIV/AIDS [4–7]. However, the lack of high-quality research has hindered the development of evidence-based clinical research on HIV/AIDS and prompted the design of this clinical trial.

This trial has the following advantages: (1) This study is a randomised, double-blind, placebo-controlled, multicentre study that is scientific and rigorous. (2) The trial design is guided by the TCM theory of clinical treatment, which is based on symptom differentiation. (3) The study participants will be selected from a region of China that has a high prevalence of HIV infection, and the long-term follow-up will ensure the compliance of the participants.

The results of this clinical trial would reveal whether TCM can supplement Western medical treatment for AIDS. If the trial is successful, it will provide a new option for patients and physicians to reduce the cost and burden of AIDS care.

## Trial status

Patient recruitment started on 1 March 2020 and will be completed on 20 December 2021. Version number:2.0.

## Data Availability

The data that support the findings of this study are openly available in the “clinical evaluation centre of the Chinese Academy of Traditional Chinese Medicine”. Data or codes generated or used during the study are available from the corresponding author by request.

